# Abbreviation

AD Alzheimers disease

ADAS-cog Alzheimer’s Disease Assessment Scale-cognitive subscale

AE Adverse Event

CDR Clinical Dementia Rating

COPD Chronic obstructive pulmonary disease

CRF Case report form

DSM-IV Dementia of the Alzheimer's type in Diagnostic and Statistical Manual of Mental Disorders, 4th edition

HAMD Hamilton Anxiety Scale

HIS Hachinski Ischemic Score

MMSE Mini-mental state examination

MRI Magnetic resonance image

NPI Neuropsychiatric Inventory

SAE Serious Adverse Event

TCM Traditional Chinese medicine

# Introduction

We conducted a 48 weeks, randomized, double-blind, double-dummy, and multicenter trial to explore the efficacy in improving cognitive function in patients with mild Alzheimer’s disease(AD) of kidney and marrow deficiency syndrome by Chinese herbal formula to tonify the kidney, company with donepezil hydrochloride (DH) (provided by Eisai China Inc. Tianjin, China). The formula is composed of Yinyanghuo (Epimedium), Nvzhenzi(Fructus Ligustri Lucidi),Buguzhi (Psoralea fruit), Heshouwu (Radix Polygoni Multiflori), Huangqi (Radix Astragali), Chuanxiong(Ligusticum wallichi Franchat), Shichangpu(Acorus gramineus)(provided by Shenzhen Sanjiu Modern Chinese Medicine limited Company, Tianjin, China).

## **Clinical efficacy evaluation of tonifying kidney essence method in treating AD**

To evaluate the clinical efficacy of tonifying kidney essence method in treating AD by total scores of traditional Chinese medical syndrome, Alzheimer’s Disease Assessment Scale-cognitive subscale (ADAS-cog), Mini-Mental State Examination (MMSE), Activity of Daily Living Scale (ADL), Neuropsychiatric Inventory (NPI), and magnetic resonance image(MRI); to evaluate the long term efficiency of tonifying kidney essence method in treating AD through investing the follow-up and end point. We try to reveal the rules of tonifying kidney essence method in treating AD and the relationship between the theory “The Kidney Stores Essence and Brain Is The Sea of Marrow” and AD, in order to set guidelines for treating AD from kidney.

## **Material basis of tonifying kidney essence method in treating AD**

1.2.1specific plasma proteins expression related outcome test

- - 1. “NEI network” related outcome test

# Patient

## **2.1 Diagnostic criteria**

### 2.1.1 Alzheimer’s disease

According to the Diagnostic criteria for 294.1x Dementia of the Alzheimer's type in Diagnostic and Statistical Manual of Mental Disorders, 4th edition (DSM-IV) (APA, 1994)：

A. The development of multiple cognitive deficits manifested by both

(1) memory impairment (impaired ability to learn new information or to recall previously learned information)

(2) one (or more) of the following cognitive disturbances

(a) aphasia (language disturbance)

(b) apraxia (impaired ability to carry out motor activities despite intact motor function)

(c) agnosia (failure to recognize or identify objects despite intact sensory function)

(d) disturbance in executive functioning (i.e., planning, organizing, sequencing, abstracting )

B. The cognitive deficits in Criteria A1 and A2 each cause significant impairment in social or occupational functioning and represent a significant decline froma previous level of functioning.

C. The course is characterized by gradual onset and continuing cognitive decline.

D. The cognitive deficit in Criteria A1 and A2 are not due to any of the following:

(1) other central nervous system conditions that cause progressive deficits in memory and cognition( e.g., cerebrovascular disease, Parkinsin's disease, Huntington's disease, subdural hematoma, normal-pressure hydrocephalus, brain tumor)

(2) systemic conditions that are known to cause dementia (e.g., hypothyroidism, vitamin B_12_ or folic acid deficieney, niacin deficiency, hypercalcemia, neurosyphilis, HIV infection)

(3) substance-induced conditions

E.The deficits do not occur exclusively during the course of delirium.

F. The disturbance is not better accounted for by another Axis I disorder(e.g., Major Depressive Disorder, Schizophrenia).

### 2.1.2 Clinic terminology of traditional Chinese medical diagnosis treatment-Syndrome(GB/T 16751.2-1997)

Syndrome of kidney and marrow deficiency: kidney-essence and marrow deficiency manifests as growth retardation, long nonunion fracture, aching lumbar, dizziness, tinnitus, obliviousness and dementia.

## **2.2 Inclusion criteria**

(1) a diagnosis of dementia of the Alzheimer’s type according to the Diagnostic and Statistical Manual of Mental Disorders, 4th edition (DSM-IV) (APA, 1994);

2) a diagnosis of Syndrome of kidney and marrow deficiency

(3) women or men aged 50–85 years;

(4) Hachinski Ischemic Score(HIS) ≤4;

(5) Hamilton Anxiety Scale(HAMD) score of ≤7;

(6)Written informed consent from all patients (or their legal representatives);

(7) Clinical Dementia Rating (CDR) score of 1.

## **2.3Exclusion criteria**

(1) with vascular dementia or any neurological disorder other than AD that contributed substantially to dementia;

(2) with severe heart, liver, kidney and blood system diseases (sinus bradycardia and atrioventricular block, AST and ALT 2 times more than the upper limit of normal value; kidney function tests showing BUN 1.5 times higher than the upper limit of normal value, Cr more than the normal value );

(3)allergies or allergic to donepezil hydrochloride and Piperidine Derivatives;

(4) the use of any drugs that may affect cognitive function 4 weeks prior to randomization;

(5) uncontrolled hypertension;

(6) with diseases that may interfere with cognitive tests such as aphasia, hemiplegia, and others(severe visual or hearing loss);

(7) with serious complications (asthma and chronic obstructive pulmonary disease(COPD));

(8) participation in another investigational new drug trial;

(9) with advanced, severe disease that could interfere with study assessments.

## **2.4 Withdrawing rules**

### 2.4.1 Withdrawn by the researchers

If further participation is a health risk for the patient, the researcher decides the patient should terminate.

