### 2.4.2 The patient decides to withdraw from the study

根据知情同意书的规定，受试者有权中途退出试验，或受试者虽未明确提出退出试验，但不再接受用药及检测而失访，也属于“退出”（或称“脱落”）。应尽可能了解其退出的原因，并加以记录。无论何种原因，对退出试验的病例应保留其病例报告表，并以其最后一次随访或检测结果转为最终结果，对其疗效和不良反应进行全数据集分析。

According to the informed consent provisions, the patient has the right to withdraw from the trial; If patients withdraw their consent for follow-up then, if at all possible, the reason for loss to follow-up should be ascertained and permission should be requested to use data collected already for the purposes of the trial.

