## **2.5 exclusion cases standard**

（1）严重违反纳入标准的病例。

(1) a serious breach of the inclusion criteria.

（2）纳入后未曾用药或无任何可评价记录的病例。

(2) no medication intake or no case evaluation recorded after screened.

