## **3.2 Patient enrollment**

Patients are recruited from three centers, 40 in the Second Affiliated Hospital of Tianjin University of TCM, 20 in the Tianjin Huanhu Hospital, and 60 in the Longhua Hospital of Shanghai University of TCM, in a 1:1 ratio.

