## **3.4 Treatment duration**

It’s a 24 weeks treatment trial.

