## **3.5 Time point**

(1) Cognitive scales: baseline (0 week), week 12(treatment), week 24(treatment), week -48(follow up);

(2) Imaging (BOLD-fMRI, magnetic resonance spectroscopy, hippocampus formation): baseline (0 week), week 12(treatment);

(3) NEI network: baseline (0 week), week 4(treatment), week 24(treatment);

(4) Safety outcomes: baseline (0 week), week 12(treatment), week 24(treatment)**;**

(5) Specific parameters related to AD: baseline (0 week), week 12(treatment).

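### Section 2.4.1 treats a researcher's health-risk stop as withdrawal, does not separate stopping study drug from leaving follow-up, and asks for no assessment at stopping

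*Protocol*

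**What the plan says.** - **Researcher-led stop.** The whole of section 2.4.1 reads: "If further participation is a health risk for the patient, the researcher decides the patient should terminate". It sits under the general heading on withdrawing, and its own heading calls the case a withdrawal by the researchers.
- **Patient-led withdrawal, English text of 2.4.2.** "If patients withdraw their consent for follow-up then, if at all possible, the reason for loss to follow-up should be ascertained". Permission is then to be sought to use the data already held. No final assessment is asked for.
- **Patient-led withdrawal, Chinese text of 2.4.2.** This adds a rule that the English lacks. Whatever the reason, a case that leaves keeps its case report form, and its last follow-up or test result becomes the final one ("并以其最后一次随访或检测结果转为最终结果"). Efficacy and adverse reactions are then analysed on the full data set.
- **Schedule, section 3.5.** "Cognitive scales: baseline (0 week), week 12(treatment), week 24(treatment), week -48(follow up" (the last entry is taken to mean week 48) and "NEI network: baseline (0 week), week 4(treatment), week 24(treatment". Safety tests are at weeks 0, 12 and 24 (3.5 and 4.1.2). Section 4.1.1 defines them as blood, urine and stool routine, ECG, ALT, AST, BUN and Cr.
- **Treatment, section 3.4.** "a 24 weeks treatment trial".
- **Adverse events, section 5.2.** After the first report the investigator must keep following the subject at later visits or contacts and arrange extra tests where indicated or requested. This continues until the event resolves, stabilises or is explained, or the subject is lost.
- **Follow-up in general, section 6.1(3).** Participants are to be followed as the protocol sets out.

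**The concern.** Stopping study drug and leaving the study are different events. A patient whose drug is stopped for safety has not refused to be seen again and can usually still be assessed. Section 2.4.1 does not make this distinction. Its heading and its trigger (participation, not drug) both point to exit, and nothing in it calls for a last measurement.

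At stake are the cognitive outcomes of patients stopped because of perceived harm. If they leave before week 12, they have no cognitive value after baseline. If the Chinese last-result rule is then applied, they enter the efficacy comparison as unchanged. Section 2.1.1 describes the disease as one of continuing decline, so an imputed zero may be kinder than what would have been observed. The three centres could also apply so brief a rule differently.

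**Working it through.** The protocol gives no figure on this point to reproduce. The check sets the stopping rule against the visit schedule.

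**Step 1. Scheduled assessments after baseline (3.5, 4.1.2).** Cognitive scales: weeks 12, 24 and 48, so 3. Safety panel with ECG: weeks 12 and 24, so 2. NEI network: weeks 4 and 24, so 2.

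**Step 2. Assessments lost per stopped patient, if 2.4.1 is followed as study exit.**

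| Time of stop | Cognitive | Safety panel and ECG | NEI |
|---|---|---|---|
| Before week 4 | 3 of 3 | 2 of 2 | 2 of 2 |
| Weeks 4 to 12 | 3 of 3 | 2 of 2 | 1 of 2 |
| Weeks 12 to 24 | 2 of 3 | 1 of 2 | 1 of 2 |

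Treatment ends at week 24, so there is no later row. The first two rows cover 12/24 = 50% of the treatment period. In both, the last scheduled cognitive, safety-panel and ECG values are baseline. The week-4 NEI sample does not fill the gap: 4.1.1 lists it under curative effect, and it contains no cognitive scale, ALT, AST, BUN, Cr or ECG.

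**Step 3. Effect of the last-result rule, if it covers researcher withdrawals.** Change = last value − baseline = baseline − baseline = 0.

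**Step 4. Scale, by assumption only.** The centre targets are "40 in the Second Affiliated Hospital of Tianjin University of TCM, 20 in the Tianjin Huanhu Hospital, and 60 in the Longhua Hospital", so 40 + 20 + 60 = 120, and 1:1 allocation gives 60 per arm. Suppose k patients in an arm stop before week 12 and would have changed by d on average. Scoring them as zero moves that arm's mean change by (k/60) × d in size:

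- k = 3: 3/60 = 5%, a shift of 0.05d.
- k = 6: 6/60 = 10%, a shift of 0.10d.

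The between-arm difference moves by (k₁d₁ − k₂d₂)/60 in size, which is zero if the two products are equal. The protocol gives neither k nor d, so this shows the form of the effect and does not estimate it.

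**Step 5. Search for a remedy elsewhere.** Section 5.2 gives continued contact and case-by-case tests after a reported adverse event, but no cognitive scale. Section 6.1(3) refers back to the protocol, which does not say what schedule applies after a researcher-led stop. No section fixes an assessment at stopping.

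**The case against.** The strongest reply is that 2.4.1 never says follow-up ends: the verb has no object. The English 2.4.2 treats withdrawing consent for follow-up as a separate act by the patient. The Chinese 2.4.2 counts as dropped out a patient who no longer accepts drug and testing. Section 6.1(3) could mean that the ordinary schedule simply continues, and 5.2 requires later contact after a reported event. On that reading drug stops and visits go on.

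This stands as a possible reading. It shows that the text is ambiguous, not that it is adequate, because heading and trigger still favour exit. Four stronger inferences that a reader might draw are therefore not supported:

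- **That all remaining scheduled outcomes are certainly lost.** The table holds only if 2.4.1 is applied as study exit.
- **That safety information disappears.** Many health-risk stops will follow a reported adverse event, and 5.2 then requires follow-up and indicated tests. What is not secured is the full panel at stopping and any cognitive scale.
- **That the patient would be excluded under 2.5(2).** The English ("no medication intake or no case evaluation recorded after screened") might suggest so. The Chinese excludes only cases never medicated or with no evaluable record of any kind, and an adverse event record or a week-4 NEI result may well count as one.
- **That the comparison is biased by a known amount or in a known direction.** Selection on perceived harm makes dependence on cognitive outcome plausible but does not establish it.

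It might also be said that this belongs in the statistical analysis plan. How withdrawn cases are analysed may, but who is still assessed after drug is stopped is a conduct rule, and no analysis recovers data that were never collected.

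**Conclusion.** The point holds as a defect of wording and conduct. Section 2.4.1 merges stopping drug with withdrawal and secures no measurement at stopping. Read naturally as exit, it leaves a patient stopped before week 12 with baseline as the last scheduled cognitive, safety-panel and ECG value. Zero cognitive change as the final result needs one further assumption: that the last-result rule, which appears only in Chinese and under the patient-decision heading, reaches researcher withdrawals. Its whatever-the-reason wording allows that but does not settle it.

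The loss is firmest for cognition and only partial for safety. The size of any bias cannot be computed from the document, and the 5% to 10% is an illustration. The change is worth making because it is cheap and keeps consenting patients under observation. The week-48 cognitive visit is already off treatment for everyone, so stopping drug early is no reason in itself to lose it.

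**What to change.** 1. **Reword 2.4.1** so that a health-risk decision stops study drug, and any study procedure that is itself a risk, but does not end follow-up. When and why to stop remains the researcher's judgement.
2. **Keep the remaining scheduled visits** unless consent for follow-up is withdrawn: cognitive scales at weeks 12, 24 and 48, and safety tests at weeks 12 and 24. Record them as off-drug and note any new cognitive treatment.
3. **Assess at stopping**, where the patient is able, with the existing cognitive scales and the existing safety panel. A patient who later leaves then has a last cognitive value other than baseline.
4. **State in both languages of 2.4.2** that the last-result rule applies only to patients who actually leave follow-up.

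Section 5.2 is unchanged. The cost is protocol and consent wording, one unscheduled assessment per stopped patient, and visits already in the schedule. The downsides are a minor visit burden and later scores that may reflect other treatment started after stopping, which is why that treatment should be recorded.

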### 2.4.2 The patient decides to withdraw from the study

根据知情同意书的规定，受试者有权中途退出试验，或受试者虽未明确提出退出试验，但不再接受用药及检测而失访，也属于“退出”（或称“脱落”）。应尽可能了解其退出的原因，并加以记录。无论何种原因，对退出试验的病例应保留其病例报告表，并以其最后一次随访或检测结果转为最终结果，对其疗效和不良反应进行全数据集分析。

According to the informed consent provisions, the patient has the right to withdraw from the trial; If patients withdraw their consent for follow-up then, if at all possible, the reason for loss to follow-up should be ascertained and permission should be requested to use data collected already for the purposes of the trial.

## **2.5 exclusion cases standard**

（1）严重违反纳入标准的病例。

(1) a serious breach of the inclusion criteria.

（2）纳入后未曾用药或无任何可评价记录的病例。

(2) no medication intake or no case evaluation recorded after screened.

# 3 Methods

## **3.1 Study design**

The randomized, double-blind, double-dummy, parallel controlled and multicenter trial designed by Cerebropathy Study Center in the Second Affiliated Hospital of Tianjin University of TCM.

## **3.2 Patient enrollment**

Patients are recruited from three centers, 40 in the Second Affiliated Hospital of Tianjin University of TCM, 20 in the Tianjin Huanhu Hospital, and 60 in the Longhua Hospital of Shanghai University of TCM, in a 1:1 ratio.

## **3.3 Intervention**

The TCM formula in our study was YHD, including Yinyanghuo (Epimedium) 10g, Nvzhenzi(Fructus ligustri lucidi) 10g, Buguzhi (Psoralea fruit) 10g, Heshouwu (Radix polygoni multiflori)10g, Huangqi (Radix astragali) 10g, Chuanxiong(Ligusticum wallichi franchat) 6g, Shichangpu(Acorus gramineus) 6g in one unit. Each herb was provided as herbal concentrate-granules in one bag and quality controlled by the Shenzhen Sanjiu Modern Chinese Medicine limited Company (Tianjin, China). Every patient in YHD group orally took 100 ml of the decoction once a day half hour after breakfast and DH-simulation 5 mg before sleep for 24 weeks. Patients in DH group orally took DH 5 mg a day before sleep provided by Eisai China Inc. (Tianjin, China), and YHD-simulation 100 ml of the decoction half hour after breakfast for 24 weeks.

## **3.4 Treatment duration**

It’s a 24 weeks treatment trial.

## **3.5 Time point**

(1) Cognitive scales: baseline (0 week), week 12(treatment), week 24(treatment), week -48(follow up);

(2) Imaging (BOLD-fMRI, magnetic resonance spectroscopy, hippocampus formation): baseline (0 week), week 12(treatment);

(3) NEI network: baseline (0 week), week 4(treatment), week 24(treatment);

(4) Safety outcomes: baseline (0 week), week 12(treatment), week 24(treatment)**;**

(5) Specific parameters related to AD: baseline (0 week), week 12(treatment).

## **3.6 Drug monitoring**

### 3.6.1 Study preparing

All the drugs are provided by the amenable administrators for the study centers.

### 3.6.2 Studying

After the participants sign informed consent, the researcher set the random number according to the sequence of recruitment; open the randomized envelope and give different drugs to patients in different groups. The drugs are locked in special Counter and stored at room temperature. The drug administrator should record the data, name of patient, random number, group, dosage, and residual drugs every distribution.

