## **6.2 Compliance**

In order to ensure the compliance of the participants, the participants should be made to fully understand the significance of this study and the importance of taking medicine on time.

(1) The participants should be asked to take medicine on time by caregivers.

(2) The drugs should be counted and the patients should return the remaining drug at follow up. Researchers should count the number of drugs, record the detailed reasons for incompletely intake, and strengthen the monitoring of poor efficacy or poor compliance of the patients.

(3) Compliance evaluation: compliance = (the actual dose / planed dose) *100%

good compliance: 80%-120% compliance

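### The dispensing procedure in Protocol 3.6.2 discloses allocation to site staff and conflicts with the double-blind declaration; nothing separates those staff from the people who assess outcomes

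*Protocol*

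**What the plan says.** The Introduction describes a "randomized, double-blind, double-dummy, and multicenter trial", and section 3.1 repeats the claim: "The randomized, double-blind, double-dummy, parallel controlled and multicenter trial". Section 3.3 supplies the means for it. The YHD arm also takes "DH-simulation 5 mg before sleep for 24 weeks", and the donepezil (DH) arm also takes "YHD-simulation 100 ml of the decoction half hour after breakfast for 24 weeks".

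Section 3.6.2 sets out what happens at the site. Once consent is signed, "the researcher set the random number according to the sequence of recruitment". The same sentence continues with the instruction to "open the randomized envelope and give different drugs to patients in different groups". The record-keeping follows: "The drug administrator should record the data, name of patient, random number, group, dosage, and residual drugs every distribution".

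On follow-up, section 6.2 states that "Researchers should count the number of drugs", record why doses were missed and watch patients with poor efficacy or poor compliance. Section 2.4.1 leaves withdrawal on health grounds to the researcher. Section 5.1 has the investigator question patients about adverse events and record them.

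**The concern.** In a working double-dummy scheme the site hands every patient the same pair of items and never has to act on the treatment group. Section 3.6.2 has the site open the allocation and choose supplies by group. It then keeps a log that ties the group to a named patient at each dispensing, so the disclosure lasts through the 24 weeks of treatment.

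The efficacy scales named in the protocol's first objective (TCM syndrome score, ADAS-cog, MMSE, ADL, NPI) are administered or scored by an assessor, some with an informant. Recording adverse events, withdrawing a patient under section 2.4.1 and excluding a case for a serious breach under section 2.5 also call for judgement. If the people doing these things know the arm, their judgements can move with it, and an analysis cannot separate that movement from a treatment effect.

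**Working it through.** No arithmetic decides this point. The check sets the relevant sections side by side and asks whether any of them repairs section 3.6.2.

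1. **What is declared.** The Introduction and section 3.1 both say double-blind and double-dummy. Neither limits the blinding to patients.

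2. **Who acts in section 3.6.2.** The researcher is the only subject named in the sentence that covers numbering, opening the envelope and giving the drugs. On its plain reading, one site person does all three. The drugs are given according to group, so the envelope conveys the group or something equivalent to it.

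3. **What is recorded.** Patient name, random number and group stand together in the drug log, renewed at every distribution. The log-keeper is a separately named role, the drug administrator.

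4. **Whether a safeguard appears elsewhere.** I looked in these places:
   - Sections 3.6.1, 3.6.3 and 3.6.4 (supply, resupply and return) do not mention coded or numbered kits.
   - Section 3.3 describes the dummies but not their labelling or packing.
   - Sections 6.1 to 6.5 (investigators, compliance, laboratory, coordination, monitors) name no independent dispenser and no blinded rater.
   - Sections 7.1 to 7.3 (data management) do not mention restricted access to the drug log or a masked group label.
   - Section 8 is a general duty of secrecy towards others.
   - No section describes an emergency code-break procedure.

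5. **Whether roles are separated.** Drug counting and the watch for poor efficacy (6.2) and the withdrawal decision (2.4.1) fall to researchers, the same term used for the person who opens the envelope. The protocol does not say who scores the scales.

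6. **Extent.** Section 3.2 plans 40 + 20 + 60 = 120 patients at three centres, and section 3.6.2 exempts none of them. All 120 allocations would be disclosed to someone at a site.

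Steps 1 to 3 establish the conflict: a stated procedure defeats a stated property for site staff. Steps 4 and 5 show that the text offers nothing to contain it.

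**The case against.** The strongest reply is that double-blinding fails only if patients or assessors learn the arm. An unblinded dispenser working beside masked raters would satisfy both sections. The protocol names a drug administrator apart from the researcher, does not say that the person opening the envelope rates anyone, and does not say whether the envelope or the log holds an arm name or a code. The English is also loose. All of this is fair, and it limits how certain the bias is. It does not remove the defect, because each of these benign readings needs a fact that the protocol does not contain, and the plain text points the other way.

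Several stronger readings are tempting and do not hold:

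- **That the double dummy is pointless.** Each arm takes one active and one simulated product, so patients and caregivers can stay masked whatever the dispenser knows.
- **That allocation concealment is weakened.** Numbering and opening come after consent and in recruitment order, which does not in itself expose upcoming assignments.
- **That counting returned drug reveals the arm.** Both arms return both products. Section 6.2 shows only that researchers handle drug.
- **That the questioning about adverse events is itself a weakness.** Section 5.1 asks for open-ended, non-leading questions as a guard against bias. The exposure lies in who asks and records.
- **That every outcome is compromised.** The NEI network, tau and amyloid measurements are assigned to one hospital (section 4.1) and the imaging to one site (section 4.2.1). These depend less on a rater's opinion than the scales do.

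**Conclusion.** The point holds for site staff: section 3.6.2 as written discloses allocation to them and cannot be squared with the double-blind claim unless a safeguard is added. This is a wrong instruction and not a missing detail. It would not normally be left to a statistical analysis plan, since dispensing and blinding belong in the protocol.

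A reader might infer that the protocol states that the raters are unblinded. It does not. Rater unblinding is the likely result of having no separation of roles, and that conclusion rests on the plain reading that the envelope and the log show the true group.

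A reader might also want a figure for the resulting bias or the inflation of the false-positive rate. The protocol gives no standard deviation for any scale and no basis for the size of a rating shift, so any such figure would only restate its own assumptions. The correction is needed because the blinded comparison depends on it, not because of any calculated error rate.

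**What to change.** Reword section 3.6.2 along these lines:

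- The supplier or sponsor prepares and codes sequentially numbered, identical-looking double-dummy kits for each centre, each holding either YHD with DH-simulation or DH with YHD-simulation.
- After consent, the researcher assigns the next kit number at that centre and opens no allocation envelope.
- The site drug log records the kit number in place of the group.
- Sealed envelopes are held only for emergency code break, and every opening is documented.

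If safeguards of this kind already operate in practice, the sponsor need only write them into the section, including who dispenses, who scores and who can see the code.

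The cost is some pre-packing and coding work and a change of wording. The simulated products already exist, and no patients, visits or measurements are added.
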